***eHealth* Home Training Program: Mounting system for in-chair use and software**

The tablet displays feedback to the participant on training activity and weekly progress relative to these targets. The tablet software incorporates over 200 video-based training elements including instruction, peer demonstration, and practice activities and games. The tablet software records all home training activity and uploads this data to a secure server. For participants without Internet access, a portable Wi-Fi hotspot device is provided. The peer trainer monitors participant progress online and may adapt the program, or follow-up with the participant, based on their progress data. Participants and peer trainers can also exchange messages when necessary, using the *eHealth* tablet (participant) and The Zoom/MS Teams platforms or email.

**Control Group.** The control group receives no specific intervention over the course of the 4-week period; this reflects “usual practice” or the typical experience of a MWC user in their provincial context. Participants are placed on a wait-list and receive the TEAM Wheels program, as described, following completion of the study (i.e. after post-treatment data collection from the Intervention group). The site Research Assistant will make contact with control group participants at the end of weeks 2 and 4 during the study period to deter attrition/drop-out. When contact is made at week 4, the Research Assistant will schedule an appointment for post-treatment data collection (week 7). Any formal MWC training received during the wait-list period will be documented for potential post-hoc analysis as a confounding variable; however, research evidence and the investigators’ clinical experience confirm that in all 3 provinces formal training is not provided once MWC users are discharged from hospital.

**Data Analysis.** After testing for assumptions and outliers, between-groups (intervention vs control) comparison of change over time will be conducted using Generalized Linear Modeling (GLM) for participation; MWC skill capacity and performance; self-efficacy; health-related quality of life; and objective MWC mobility parameters ( $\alpha = 0.05$ ). Variables previously identified in the literature as relevant covariates (i.e. age and function as measured by baseline WST-C) will be controlled for. Model fit ( $R^2$ ), regression coefficients ( $CI_{95\%}$ ), and effect sizes ( $F^2$ )

will be assessed with Maximum Likelihood methods. Data will initially be disaggregated by sex and gender; if analyses prove non-significant, the data will be reaggregated. A repeated-measures ANOVA will be used to evaluate retention of outcomes at follow-up for treatment group participants. Additional post-hoc sub-analyses will investigate the impact of site (using 2-way ANOVA) and length of MWC use covariate (using ANCOVA), although the study is powered only for the primary analysis. Descriptive data will report on recruitment by sex, relative to prevalence data for MWC use to inform generalizability of findings and health services equity balance.

**Sample Size.** The combined results of our feasibility studies found a large effect size ( $f = 0.47$ ) for the WhOM and correlation between measures ( $R^2$ ) was 0.63. Using a comparable effect size ( $f = 0.45$ ) and measure correlation (0.6),  $\alpha = 0.05$ , and 90% power for a between-factors ANOVA repeated measures design, a sample size of 42 is required (G\*Power v.3.1.9.2). Adjusting for 20% loss to attrition, a total sample size of 54 was determined (i.e. 27 per group; intervention and control). We anticipate recruiting 1-2 participants/per site/per month, estimating 12 months required to recruit the sample. Incorporating the treatment and 6-month follow-up periods, the maximum data collection period should be 19 months. While we have built in a 20% attrition rate, our feasibility studies reported 5-10% drop-out rates, (Best et al., 2017; Giesbrecht & Miller, 2017) and with the provision of the TEAM Wheels program to control group participants after data collection, we anticipate little attrition.

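### The protocol ties the primary model's 95% confidence intervals to maximum likelihood; with 43 to 51 completers and no degrees-of-freedom correction, they would be slightly too narrow

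*Protocol*

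**What the plan says.** The Data Analysis paragraph plans a between-group "comparison of change over time will be conducted using Generalized Linear Modeling (GLM") for participation (the primary outcome) and for the secondary outcomes, at α = 0.05. Two covariates are named: "age and function as measured by baseline WST-C) will be controlled for".

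The next sentence lists what the model will report: R², "regression coefficients ( $CI_{95\%}$ ), and effect sizes ( $F^2"). It then says that these "will be assessed with Maximum Likelihood methods".

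The paragraph names no residual-variance estimator, no degrees-of-freedom correction and no reference distribution (normal, t or F). It also does not say whether the intervals are Wald or profile-likelihood.

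The Sample Size paragraph starts from "90% power for a between-factors ANOVA repeated measures design", which gives 42 participants, raised to 54 for 20% attrition. The same paragraph reports 5–10% drop-out in the feasibility studies and expects few losses.

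**The concern.** For a continuous outcome with normal errors, maximum likelihood and least squares give the same coefficients. They differ in the residual variance. Maximum likelihood divides the residual sum of squares by n and takes no account of the p coefficients already fitted. In a large trial this is invisible. With about 43 to 51 completers it shortens the standard error by 4–5%. If the analysis then also uses 1.96 in place of the t quantile, the interval shrinks further.

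At stake is the calibration of the primary result: a 95% interval that covers somewhat less than 95% of the time, and a test at a nominal 5% that rejects somewhat more often under the null. This would matter mainly if the primary result were borderline.

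The point goes beyond a detail left open for a statistical analysis plan. The protocol names an estimation method and attaches it to the confidence intervals.

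**Working it through.** **Inputs from the protocol**
- α = 0.05 (Data Analysis; Sample Size). Sidedness is not stated; two-sided is used here.
- Covariates: age and baseline WST-C. With intercept and group, p = 4.
- N = 54 with a 20% attrition allowance: 54 × 0.80 = 43.2, so about 43 completers.
- Feasibility drop-out of 5–10%: 54 × 0.90 = 48.6 and 54 × 0.95 = 51.3, so about 49 to 51 completers.

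**Assumptions**
- Normal errors and identity link.
- One post-treatment or change value per participant.
- The maximum likelihood variance is used uncorrected.

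**The plan's own figure**

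For a two-group, between-factor repeated-measures F test, the noncentrality is λ = f²·N·m / [1 + (m − 1)ρ] on 1 and N − 2 degrees of freedom. With f = 0.45, ρ = 0.6, N = 42 and m = 3 measurements:

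λ = 0.2025 × 42 × 3 / 2.2 = 11.60, and power = 0.914.

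N = 42 is reproduced. With m = 2 the answer is 44, a difference too small to matter here. For attrition, 42 / 0.80 = 52.5, so 53; 18 at each of three sites makes 54. The planning test is therefore an F test with finite degrees of freedom.

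**Effect of the uncorrected variance**

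1. Variance ratio: (RSS/n) / (RSS/(n − p)) = (n − p)/n. At n = 43, p = 4 it is 39/43 = 0.907.
2. Standard-error ratio: r = √0.907 = 0.952.
3. The correctly scaled statistic follows t with n − p degrees of freedom, so the exact two-sided error at critical value c is 2·[1 − T₍ₙ₋ₚ₎(c·r)].
   - t reference: c = 2.023, c·r = 1.926, error = 6.1%. The width ratio is r = 0.952, so the interval is about 5% too narrow.
   - Normal reference: c = 1.960, c·r = 1.867, error = 6.9%. The width ratio is 1.867/2.023 = 0.923, so the interval is about 8% too narrow.
4. The same formula at other numbers of completers, p = 4:

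| Completers | SE ratio | Error, t reference | Error, normal reference | Width, normal reference |
|---|---|---|---|---|
| 43 (20% attrition) | 0.952 | 6.14% | 6.95% | 0.923 |
| 49 (10%) | 0.958 | 5.99% | 6.68% | 0.933 |
| 51 (5%) | 0.960 | 5.95% | 6.61% | 0.935 |
| 54 (none) | 0.962 | 5.89% | 6.51% | 0.939 |

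5. Simulation check: 20,000 null data sets at n = 43, p = 4 gave 6.97% for maximum likelihood with the normal reference. RSS/(n − p) with t gave 5.1% on the same data sets.

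**The case against.** The strongest reply is that the protocol does not fix the choices that produce the error. Maximum likelihood coefficients equal least squares in this model. The sentence can therefore be read as compatible with RSS/(n − p) and t-based intervals, and many analysts would apply that correction without comment. Scale estimator and degrees of freedom are often left to a statistical analysis plan, which is not at hand. This stands to the extent that the inflation must be stated conditionally. It does not remove the point, because the method that the protocol does name, followed literally, is the one with the small-sample bias, and the correction is nowhere mentioned.

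Three stronger readings are tempting, and the document does not support them:
- **The primary test exceeds its α of 0.05.** This cannot be stated as fact. It follows only if the variance is left uncorrected. The normal reference behind the larger figures is an added assumption: the protocol names neither a test statistic nor analysis software.
- **A larger model makes it worse.** More coefficients would widen the gap, but the named covariates are age and baseline WST-C only. Site is assigned to a post-hoc two-way ANOVA, and baseline WhOM is not listed as a covariate.
- **43 is the expected number analysed.** It is the planning allowance. The protocol itself expects fewer losses, which is why the 49 to 51 range is shown beside it.

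The data structure behind a comparison of change over time is also not specified, so the percentages belong to the single-value-per-participant model assumed above.

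**Conclusion.** The point holds in a limited, conditional form and is of low severity. With the stated covariates, the maximum likelihood variance alone adds about 1 percentage point to the type I error. Adding a normal reference brings the excess to between 1.6 and 1.9 points over the range from 51 to 43 completers. Even with no attrition it does not vanish.

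The estimated group difference is not biased, and the sample size needs no change. The conclusion rests on four coefficients, normal errors, one analysed value per participant, and a literal reading in which no degrees-of-freedom correction is applied.

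**What to change.** Replace the maximum likelihood sentence in the Data Analysis paragraph. State that continuous outcomes are analysed by ordinary least squares, with residual variance RSS/(n − p) and with 95% confidence intervals and p-values from the t distribution on n − p degrees of freedom. If a repeated-measures mixed model is used instead, specify restricted maximum likelihood with a small-sample degrees-of-freedom correction such as Kenward–Roger; otherwise this is not needed.

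The cost is one sentence and a software setting, made before analysis. Compared with uncorrected maximum likelihood at 43 completers, intervals become about 5% wider with a t reference (1/0.952 = 1.05) or about 8% wider than normal-based ones (1/0.923 = 1.08). Recruitment and data collection are untouched.

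### Pooling of the primary comparison depends on an unnamed significance test by sex and gender, so the comparison the trial is sized for need not be the reported primary result

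*Protocol*

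**What the plan says.** The Data Analysis paragraph sets a between-group "comparison of change over time will be conducted using Generalized Linear Modeling (GLM) for participation", which is the primary outcome, and for the secondary outcomes, at α = 0.05 with age and baseline wheelchair skill as covariates. The same paragraph then states: "Data will initially be disaggregated by sex and gender; if analyses prove non-significant, the data will be reaggregated". Only after that come the site and length-of-use analyses. These are called post-hoc, with the remark "although the study is powered only for the primary analysis". The sex and gender step carries no such label.

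The Sample Size paragraph plans one two-group comparison: "90% power for a between-factors ANOVA repeated measures design, a sample size of 42 is required", at f = 0.45 and a correlation of 0.6. It continues: "Adjusting for 20% loss to attrition, a total sample size of 54 was determined", that is 27 per group. The Hypotheses and Primary Objectives are also stated for the two whole groups. The Methods paragraph stratifies randomisation by site only.

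**The concern.** The sentence fixes an order: split first, and pool only after a non-significant result. That makes the pooled comparison, the only one the trial is sized for, conditional on an earlier test. It does not say which test must be non-significant, and it does not say that the pooled result is reported if that test is significant.

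Two things are at stake. First, several tests at 5% can lead to the primary claim, so its error rate may exceed the stated level. Second, the headline estimate could be a sex-specific one from part of the sample, selected because it reached significance. Non-significance in about 42 people is also weak evidence that the sexes respond alike, so it is a poor licence to pool.

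**Working it through.** **Inputs from the protocol.** α = 0.05; f = 0.45; correlation ρ = 0.6; 90% power; N = 42 evaluable, 54 with 20% attrition; 1:1 allocation.

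**Assumptions.** Two sexes; share of women 33–50% (the protocol gives none; 30% changes the error rates very little); normal outcome; two-sided t tests without covariates; every test at 5%.

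**1. The plan's own figure.** For a between-factors repeated-measures ANOVA with m measurements, λ = f²·N·m / [1 + (m − 1)ρ] on 1 and N − 2 degrees of freedom.
- m = 2, N = 42: λ = 0.2025 × 42 × 2 / 1.6 = 10.6, power 88.9%; 90% needs N = 44.
- m = 3, N = 42: λ = 0.2025 × 42 × 3 / 2.2 = 11.6, power 91.4%; 90% needs N = 41, or 42 when made even.
- Attrition: 42 / 0.8 = 52.5, so 53; 54 is the next even number and divides by three sites.

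The figure is reproduced to within two participants, as a single pooled comparison.

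**2. False-positive rate with no treatment effect.** The pooled test alone gives 5.0%.

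| Gate | Procedure | False-positive rate |
|---|---|---|
| A. Treatment test within each sex | Claim if either is significant; otherwise test pooled | about 11–12% |
| B. Sex-by-treatment interaction | Sex-specific tests if significant; otherwise pooled | about 8% |
| C. Sex main effect, sexes equal | Sex-specific tests if significant; otherwise pooled | about 5% |
| C. Sex main effect, sexes differ by 0.5–1.0 baseline SD | As above | about 7–9% |

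Simple arithmetic agrees with the simulations:
- A: the two sex-specific tests alone give 1 − 0.95² = 9.75%; the pooled fallback adds about 2 points.
- B: the gate opens in 5% of null trials, and a sex-specific test is then significant in about 65% of them. So 0.05 × 0.65 + 0.95 × 0.05 = 0.0325 + 0.0475 = 8.0%.
- C, sexes equal: 0.05 × 0.0975 + 0.95 × 0.05 = 0.0049 + 0.0475 = 5.2%. As the true sex difference grows, the gate opens more often and the rate moves towards the 9.75% of two separate tests.

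**3. Power at the design effect (m = 2).**
- One sex alone, 42 split 20/22: λ = 0.2025 × 20 × 2 / 1.6 = 5.06, power 57%; λ = 0.2025 × 22 × 2 / 1.6 = 5.57, power 61%.
- Whole procedure, chance of any positive result: about 91% under A and about 89% under B, against about 89% for the pooled test alone.

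Under A, at least one sex-specific test is significant in about 83% of trials at the design effect. In most successful trials the rule would therefore stop before the pooled comparison.

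**The case against.** The best defence is that the hypothesis, objectives and sample size are all stated for whole groups, and that the protocol says it is powered only for the primary analysis. On that view the pooled comparison is plainly the intended primary result. The background section gives a benign motive for looking at sex: women may start with lower self-efficacy, yet training benefits both sexes. If the pooled test is always reported, its error rate stays at 5%. This shows a sensible intention, but the operative sentence says something else. It makes pooling conditional, and no other sentence overrides it. The point also does not depend on a missing analysis plan: the protocol states a rule, and a plan that followed it would inherit the fault.

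Some stronger readings are tempting but are not supported:
- *The 5% level is lost however the sentence is read.* With a sex main-effect gate and no true sex difference, it is nearly kept.
- *The pooled result will never appear once the gate opens.* The protocol does not say so; it only fails to require that result.
- *Power falls from 90% to about 60%.* That compares one sex-specific test with the whole trial. The procedure as a whole gives a positive result about as often as the pooled test. An interaction gate also uses every participant, so the first step need not rest on half the sample.
- *Adding gender raises the error to 18.5%.* That figure assumes four independent tests (1 − 0.95⁴). Splits by sex and by gender would largely reuse the same people, so it should not be relied on.

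**Conclusion.** The concern holds as a defect in a stated rule. A significance test decides whether the primary comparison is pooled, and the pooled comparison is not guaranteed to be the reported primary result. Against the stated 5%, the false-positive rate runs from about 5% to about 12%, depending on which test is the gate and, for a main-effect gate, on whether the sexes truly differ. The protocol does not settle which reading applies, so no single figure should be quoted as the error rate. The range rests on the assumptions of about 42 completers, 33–50% women and unadjusted tests at 5%.

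The loss is in error control and in the selection of the headline estimate, not in the overall chance of a positive trial. Sex-specific estimates, at about 57–61% power each for a near-even split, should not replace the pooled result. The sample size itself is not in error; it is valid for the pooled comparison.

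**What to change.** Replace the sentence in the Data Analysis paragraph with:

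> The pooled, covariate-adjusted treatment comparison is the single primary analysis and is reported at alpha 0.05 whatever the sex and gender results. Sex- and gender-disaggregated estimates, and treatment-by-sex and treatment-by-gender interactions with 95% CIs, are reported as supportive analyses and do not determine whether data are pooled.

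This costs one sentence. The sex and gender reporting is kept, and the sample size, data collection and conduct do not change. The simulated false-positive rate of the primary claim returns to 5.0%.

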A peer, who has experiential knowledge and similar characteristics as the target population, can cultivate social connections through sharing of realized knowledge. Peer-led training is feasible to administer and effectively improves wheelchair skills, self-efficacy, and satisfaction with participation. Providing *eHealth* training at home fosters autonomy (i.e., choice and volition), while peers enhance feelings of competence (i.e., self-efficacy) and relatedness (i.e., feeling connected). When these three needs are satisfied, autonomous motivation (i.e., engaging in an activity by choice) increases, driving behaviour change and maintenance, such as wheelchair use and social participation. Every province and territory in Canada has implemented delivery of *eHealth*, providing potential partnership opportunities for TEAM Wheels. By integrating a peer-led approach with the *eHealth* training program, we are leveraging two novel strategies. This is a contemporary approach to community rehabilitation with MWC users that builds on innovations we have already developed in Canada. The results of this trial will provide evidence to move forward with implementation of service at the regional health care delivery level. Furthermore, access to TEAM Wheels has the potential for future exploration in the context of rural and remote service delivery, where consumers have even greater restriction to health care access.

**Purpose.** Our purpose is to *evaluate the effect* of a 1-month, peer-led *eHealth* training program (TEAM Wheels) on satisfaction with activity participation and related rehabilitation outcomes among individuals transitioning to MWC use, compared with current wheelchair training practice.

**Hypotheses:** We hypothesize that at post-treatment, the primary outcome of wheelchair-related participation will be significantly higher in the TEAM Wheels group and that post-treatment improvements will be retained at 6-month follow up. We also hypothesize that the TEAM Wheels program will demonstrate clinically and statistically significant differences at post-treatment and at 6-month follow up on secondary outcome measures of wheelchair-specific self-efficacy; skill capacity and performance; health-related quality of life; and objective measurement of mobility.

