**Objectives:****Primary Objectives: Participation**

1. To measure the effect of TEAM Wheels on *satisfaction with participation* in important activities of life compared to current practice;
2. To measure retention of participation benefits at 6-months post treatment.

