## Methods:

**Research Design.** This RCT employs 3 sites (Vancouver, Winnipeg, Quebec City) comparing a 4-week MWC training intervention and wait-list control group among individuals transitioning to MWC use. TEAM Wheels will be delivered in the community specifically targeting new users, defined in the literature as individuals within one year of receiving their MWC.

**Methods.** Participants will be randomly assigned to the TEAM Wheels or control group using a 1:1 allocation ratio between groups. To support balance between groups and masking of assignment, our statistician ([name]. – Quebec City) will create a computerized randomization process with undisclosed block size. Randomization will be stratified by site to ensure comparable treatment group size ( $n \sim 18$  per site). Given the potential benefits of the intervention already reported in our previous studies, control group participants will also receive the TEAM Wheels intervention following a 4-week control period and post-treatment data collection (they will be on a “wait-list” for the TEAM Wheels program and receive **no intervention** during the study period).

Following enrolment, baseline data will be collected and entered into a secure MS Teams database. MS Teams data storage is approved by the University of Manitoba Health Research Ethics Board (HREB) and is *Personal Health Information Act* (PHIA)/*Freedom of Information and Protection of Privacy Act* (FIPPA) compliant. The site Research Assistant (RA) will then obtain the participant’s group assignment and coordinate timing for the first teleconference peer trainer session conducted via the computer tablet; for treatment group assignments this will occur as soon as is practical and for control group assignments this will be scheduled after blinded post-treatment data collection is complete. The Research Assistant will also arrange blinded follow-up (retention) data collection for treatment group participants 6 months after post-treatment data collection. Although collecting 6-month retention data for the control group would be optimal, delaying a potentially beneficial intervention and the associated risk of participant attrition make this option undesirable.

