**Outcome measures.** At baseline, descriptive characteristics including age, sex, gender, marital status, highest level of education, primary diagnosis related to MWC use, and length of time using the MWC will be collected. Five outcome measures (available in both French and English) will be administered at baseline, post-treatment, and (for treatment group participants) at 6-month follow-up. The RA will complete the questionnaires with the participant via telephone or Zoom/MS Teams teleconference. The participant will be provided with the questionnaire in advance, via post or email. The RA will collect the data by telephone or teleconference and (subsequently) enter it into a password protected Excel file in the MS Teams database.

*Satisfaction with Participation (primary outcome).* The International Classification of Functioning, Disability and Health (ICF) identifies participation as “involvement in a life situation,” including the subjective experience and performance of important activities and roles. The Wheelchair Outcome Measure (WhOM) is a patient-oriented measure of satisfaction with participation, specifically related to relevant activities inside and outside of the home. The WhOM

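### Retention at 6 months is a primary objective, but the repeated-measures ANOVA named for it in the treated arm, with no contrast or criterion, cannot show that a gain was kept

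*Protocol*

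**What the plan says.** The second primary objective (Protocol, Primary Objectives: Participation) reads "To measure retention of participation benefits at 6-months post treatment". The matching hypothesis (Protocol, Hypotheses) is that "post-treatment improvements will be retained at 6-month follow up".

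The analysis is one sentence in Protocol, Data Analysis: "A repeated-measures ANOVA will be used to evaluate retention of outcomes at follow-up for treatment group participants". It does not say which visits enter the ANOVA, which comparison decides, or what result counts as retention.

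Outcomes are measured "at baseline, post-treatment, and (for treatment group participants) at 6-month follow-up" (Protocol, Outcome measures), so the treated arm has three occasions and the control arm two. The Methods section explains the gap openly: "Although collecting 6-month retention data for the control group would be optimal", it was judged undesirable because it would delay treatment and risk attrition.

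For the secondary outcomes, the Hypotheses paragraph nevertheless expects that "the TEAM Wheels program will demonstrate clinically and statistically significant differences at post-treatment and at 6-month follow up on secondary outcome measures".

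**The concern.** The question behind the objective is whether the score at 6 months is still close to the score after treatment. A repeated-measures ANOVA over baseline, post-treatment and follow-up tests whether all three means are equal. A gain at post-treatment is enough to reject that, whatever happens afterwards, so significance does not mean retention. If the ANOVA is restricted to post-treatment and follow-up, retention would have to be read from a non-significant result, which in 21 to 27 people may reflect only low power.

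The hypothesis wording adds a second problem. It uses one phrase for post-treatment, where the Data Analysis section compares randomised groups, and for 6 months, where no group comparison can be made. Participants are within 12 months of their first wheelchair, so change in the treated arm alone cannot be separated from ordinary adaptation.

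At stake is a claim on a primary objective resting on a result that looks the same whether the benefit lasted or disappeared.

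**Working it through.** **Inputs from the Protocol.** Evaluable sample 42, 1:1, hence 21 treated completers; 27 treated enrolled (Sample Size). Correlation between measures 0.6 (Sample Size). Expected WhOM gain 2.3 points, d = 0.93, clinically meaningful change 1.6 points (Outcome measures).

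**Assumptions.** No WhOM SD is stated. Reading d as gain over SD gives 2.3/0.93 = 2.47; I use 2.0 to 3.0 as a range. I also assume equal variances and equal correlations across visits.

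**The plan's own figure.** For a between-factors repeated-measures ANOVA with f = 0.45, ρ = 0.6 and m occasions, λ = f²Nm/(1+(m−1)ρ). At N = 42:
- m = 3: λ = 0.2025×42×3/2.2 = 11.6, power 0.914; 42 is the smallest equal-arm sample reaching 90%.
- m = 2: λ = 0.2025×42×2/1.6 = 10.6, power 0.889; 44 would be needed.

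So 42 is reproduced to within two participants. 42/0.8 = 52.5, rounded up to 54 for equal arms and sites. This point does not dispute the sample size.

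**Reading 1: time effect over three visits.** λ = n·Σ(μₜ−μ̄)²/(SD²(1−ρ)), with 2 and 2(n−1) degrees of freedom.
- Gain fully kept, means (0, d, d): Σ = d²(4/9+1/9+1/9) = (2/3)d².
- Gain fully lost, means (0, d, 0): Σ = d²(1/9+4/9+1/9) = (2/3)d².

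The two are identical, so power is identical for any d, SD, ρ or n. With d = 2.3, n = 21, SD 2.47: λ = 21×3.527/(6.10×0.4) = 30.3.

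| n | SD 2.0 | SD 2.47 | SD 3.0 |
|---|---|---|---|
| 21, kept or lost | >0.999 | 0.999 | 0.981 |
| 27, kept or lost | >0.999 | >0.999 | 0.996 |

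The high rates need a real post-treatment gain; with no gain the rate is 5%. With a 1.6-point gain at SD 2.47 they are 0.92 (n = 21) and 0.97 (n = 27), again the same for kept and lost.

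**Reading 2: post-treatment against follow-up only.** SE = SD·√(2(1−ρ)/n). At SD 2.47, n = 21: 2.47×√(0.8/21) = 0.482. Probability that a true loss of half the gain (1.15 points) is not significant at two-sided 5% (noncentral t):

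| n | SD 2.0 | SD 2.47 | SD 3.0 |
|---|---|---|---|
| 21 | 20% | 38% | 54% |
| 27 | 10.5% | 26% | 43% |

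**What an interval gives instead.** The 95% half-width for follow-up minus post-treatment at SD 2.47 is 2.086×0.482 = 1.01 points (n = 21) or 0.87 (n = 27). Suppose retention is claimed when the lower limit lies above −1.6:
- no true loss: claimed in 88% (n = 21) or 95% (n = 27); over the SD range 97% to 74%, and 99% to 85%;
- half the gain lost: still claimed in about 14% (n = 21);
- whole gain lost: claimed in about 0.1% or less.

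A margin of 1.6 is 1.6/2.3 = 70% of the expected gain and would allow a residual benefit of 0.7 points, below the Protocol's own meaningful change. A margin of half the gain would be claimed under no true loss with the complement of the Reading 2 figures: at SD 2.47, 62% (n = 21) or 74% (n = 27).

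**The 6-month hypothesis.** Controls are offered the program after their post-treatment assessment and have no 6-month visit. The between-group difference at 6 months therefore has no data, and only within-group change can be estimated.

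**The case against.** The strongest reply is that the Protocol never says the overall F-test decides retention, or that a significant result means the gain was kept. Contrasts and criteria are commonly left to a statistical analysis plan, and none was available here. This stands as far as it goes: a reader might infer that the Protocol fixes an overall time test as its decision rule, but the text says only that a repeated-measures ANOVA will be used. The three-visit time effect is the natural reading, not a stated one. It does not remove the point, because the Protocol does name a test for a primary objective, and neither plausible reading of that test answers the question. A third reading, baseline against follow-up, would show some remaining gain, not that the post-treatment gain was kept.

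Second, the missing control follow-up is disclosed and reasoned. A reader might infer a design error, or a planned between-group test at 6 months. Neither is supported: the objectives speak of measuring retention, the primary hypothesis is worded within group, and the follow-up analysis covers treated participants only. Only the secondary-outcome sentence of the hypotheses is at fault.

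Third, 21 completers is the pessimistic case. The Protocol expects 5–10% drop-out, and the earlier peer-led work kept 87.5% at follow-up (0.875×27 = 23.6). This is fair, and the n = 27 rows bound it.

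Two further inferences fail. The Protocol does not say that participants missing a visit are excluded. A seasonal shift in wheelchair activity cannot be sized, and recruitment is spread over about 12 months.

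**Conclusion.** The point holds. The ANOVA named for the second primary objective cannot distinguish a kept gain from a lost one if it is the three-visit time effect. If it is the post-treatment versus follow-up comparison, it would mistake low power for retention in 20% to 54% of trials (n = 21) or 10.5% to 43% (n = 27) when half the gain has gone. The equality of power under full retention and full loss is algebraic under equal variances and correlations and does not depend on the assumed SD. The percentages do depend on it, and on a correlation of 0.6 and a 2.3-point gain.

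The 6-month part of the secondary hypothesis cannot be tested as a group difference and needs rewording.

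This should be fixed before analysis. It does not threaten the randomised comparison at post-treatment, and it does not show that a false retention claim will be made, only that the stated analysis would not guard against one.

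**What to change.** 1. In Data Analysis, replace the repeated-measures ANOVA with a mixed model for repeated measures in all treated participants. Report follow-up minus post-treatment and follow-up minus baseline, each with a 95% confidence interval.
2. Base any claim of retention on the interval for follow-up minus post-treatment against a margin fixed in advance and justified by the sponsor. For the WhOM, 1.6 points is at most an upper limit for that margin. Read the follow-up-minus-baseline interval beside it, so that a small residual benefit is visible. Do not base the claim on significance or non-significance of the ANOVA. Where no margin can be justified, report estimates and intervals without a claim of retention.
3. In Hypotheses, limit the between-group difference on secondary outcomes to post-treatment. Label all 6-month results as uncontrolled within-group change, with no causal claim.

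Cost: wording and minor analysis work, with no new visits or participants. The 6-month claim becomes less favourable, and a margin tighter than 1.6 points lowers the chance of being able to claim retention even when nothing is lost.
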